### Description of Patient Measures

#### Summed symptom severity score

(source: patient baseline, 10 week, and 14 week surveys). A summed symptom score will be generated based on the sum of symptom severity scores (scored 0-10) across the 8 core symptoms.

#### Adherence to chemotherapy

(source: medical record audit). Adherence to chemotherapy will be determined by the total number of dose reductions, infusion delays, and agent discontinuations.

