The current protocol describes an ongoing randomized trial designed to address these gaps in the literature by developing and evaluating an intervention that provides cancer patients and caregivers with the information they need to make effective management decisions, decrease symptom burden, and improve patient and caregiver outcomes. The study was funded by the VA Health Services Research and Development Service and began October, 2009. The trial will be completed in August 2013.

The intervention uses a Web-enabled program to alert caregivers of patients' symptoms and provide them with a framework for identifying problems, receiving structured advice, and following up to assist the patient in manage symptoms while receiving chemotherapy. Specifically, the intervention includes weekly, automated telephonic symptom assessment with self-management support calls to patients paired with Web-based caregiver alerts that include customized advice. The study will enroll 300 patients with solid tumors undergoing chemotherapy identified from two Department of Veterans Affairs (VA) outpatient oncology clinics. Patients are recruited along with an informal caregiver willing to play a limited role in assisting the patient with symptom management. The impact of the intervention will be evaluated relative to a control arm in which patients receive automated telephonic symptom assessments and self-management advice without any involvement of their identified caregiver. Thus this is one of the few rigorously designed interventions that tests the value added impact of engaging informal caregivers in symptom management for patients with cancer. Specific study hypotheses are as follows:

*Hypothesis 1a: Patients receiving automated telephonic symptom assessment and management advice, with Web-based feedback to inform and engage a caregiver, will report less frequent and less severe symptoms at 10 and 14 weeks when compared to patients receiving automated telephonic symptom assessment and management advice alone. Intervention-group patients will also report better physical function, fewer outpatient visits and hospitalizations related to symptoms, and greater adherence to chemotherapy*.

*Hypothesis 1b. The effect of the intervention on symptom severity, physical functioning, and utilization of services will be partially mediated by improved patient self-efficacy and actualized social support*.

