## Methods

The intervention's efficacy is being evaluated using a randomized, controlled trial among patients undergoing a course of chemotherapy at two Department of Veterans Affairs (VA) oncology clinics located in Ann Arbor, MI and Fargo, ND. Three hundred patients with solid tumors undergoing chemotherapy and reporting at least one core symptom at a moderate level are being assigned to either 10 weeks of weekly ATSA contacts or 10 weeks of weekly ATSA contacts plus caregiver alerts and access to the Cancer CarePartners website. The duration and intensity of the intervention is premised on past work suggesting that ATSA's benefits peak at 10 weeks [11].

The goal of the study is to determine if, when compared to a comparison group receiving ATSA alone, patients who receive ATSA and whose caregivers receive access to Cancer CarePartners will report: significantly less total symptom severity; and secondarily improved physical functioning, adherence to chemotherapy, and more appropriate utilization of health services at 10 weeks. The study also will determine whether caregivers provide more social support and report less caregiver burden and distress.

Patients and caregivers will be surveyed at intake, 10, and 14 weeks. Further, we will track patient participation with ATSA and (in the experimental arm) caregiver use of the Website and social support provided, allowing for indicators of intervention dose to be incorporated into our analyses. Finally, all patients will receive routine oncology, hospice, and/or palliative care.

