#### Chart review

A registered nurse reviews the patient's electronic medical record at week 14 or following withdrawal or death to assess covariates (e.g. comorbidities, supportive care received) and secondary outcomes (utilization, adherence with chemotherapy, and adverse events). The nurse reviews all inpatient and outpatient oncology notes written from four weeks prior to 14 weeks after informed consent. All modalities of cancer treatment and adjunct supportive care received during the observation period are noted (including consultations from palliative care services or referrals to hospice or home health nursing). Surgical procedures, the dose and duration of radiation treatment, and the dose and duration of chemotherapy (both recommended and actualized) will be noted, as will any medication changes (and reasons thereof).

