#### Utilization of services

(source: medical record audit). The utilization of inpatient and outpatient services will be measured in terms of the number of cancer-related: hospitalizations, visits to emergency or urgent care, scheduled and unscheduled contacts with oncology (in person or by phone), and referrals to home health or hospice.

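### The service-use count does not match Hypothesis 1a, and the adherence count has no denominator, so scheduled contacts and early death can distort both secondary outcomes

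*Protocol article*

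**What the plan says.** In the protocol article, Hypothesis 1a (Background) predicts for the intervention arm "fewer outpatient visits and hospitalizations related to symptoms, and greater adherence to chemotherapy". The opening of Methods words the utilisation aim differently, as "more appropriate utilization of health services at 10 weeks".

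The Utilization of services section defines the measure: "The utilization of inpatient and outpatient services will be measured in terms of the number of cancer-related: hospitalizations, visits to emergency or urgent care". The list goes on to "scheduled and unscheduled contacts with oncology (in person or by phone), and referrals to home health or hospice". The Adherence to chemotherapy section reads: "Adherence to chemotherapy will be determined by the total number of dose reductions, infusion delays, and agent discontinuations". Neither definition refers to treatment planned, time observed or time alive.

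Both outcomes come from the medical record. The Chart review section has a nurse carry out the review "at week 14 or following withdrawal or death", covering oncology notes from 4 weeks before consent to 14 weeks after it. In the same review, "the dose and duration of chemotherapy (both recommended and actualized) will be noted". The Hypothesis Testing section says that these secondary outcomes will be analysed much like the primary one, by regression adjusted for baseline. The Preliminary Analysis section allows generalized linear models where transformation fails.

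**The concern.** A secondary outcome should move in the direction its hypothesis predicts when the treatment works. These two may not.

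For utilisation, the hypothesis is about symptom-related use but the measure is about cancer-related use. Scheduled oncology contacts are part of being on chemotherapy, so a patient who is helped to stay on treatment accrues more of them. One predicted benefit then raises a quantity that is meant to fall. Home health and hospice referrals are in the same list, and the article does not say whether more or fewer would be favourable.

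For adherence, the three event types count equally and are not set against the treatment recommended. The score therefore cannot show how much of the course was given. A patient who dies early has less time in which to accrue events and so scores as more adherent and a lighter user of services. Late-stage patients are eligible, so some deaths before week 14 are plausible.

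**Working it through.** The article gives no event rates for either outcome, so there is no figure to reproduce. The rates below are assumptions, shown over a range. The window is the 14 weeks after consent.

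**1. Definition against hypothesis.** Hypothesis 1a: visits and hospitalisations related to symptoms, fewer is better. Utilisation measure: cancer-related use, scheduled contacts and referrals included. Methods: more appropriate use. These are three different targets, and a count alone cannot show appropriateness.

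**2. Weight of scheduled contacts.** Let s be scheduled and u unscheduled contacts per week. The scheduled share is s/(s + u).
- Lowest, s = 1/3 and u = 0.2: 0.333/0.533 = 62.5%.
- Middle, s = 0.5 and u = 0.1: 0.5/0.6 = 83%.
- Highest, s = 1 and u = 0.05: 1/1.05 = 95%.

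Take a patient who stays on treatment to week 14 rather than stopping at week 6, and assume that scheduled contacts cease on stopping (an upper bound). Staying on adds 8s contacts. Removing every unscheduled contact over 14 weeks would save 14u.
- Middle: 8 × 0.5 = 4.0 added against 14 × 0.1 = 1.4 saved, so the total rises by 2.6.
- Lowest share: 2.67 added against 2.8 saved, a fall of 0.13.
- Highest share: 8.0 added against 0.7 saved, a rise of 7.3.

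This is for a patient kept on treatment. The effect on an arm mean depends on how many such patients there are.

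**3. Adherence and early stopping.** Let λ be reductions plus delays per week on treatment, and a the number of agents stopped. Expected scores are 14λ for a full course, 6λ + a for stopping at week 6, and 6λ for death at week 6 with no discontinuation charted.

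| λ | Full 14 weeks | Stop at week 6, one agent | Stop at week 6, two agents | Death at week 6 |
|---|---|---|---|---|
| 0.05 | 0.7 | 1.3 | 2.3 | 0.3 |
| 0.1 | 1.4 | 1.6 | 2.6 | 0.6 |
| 0.2 | 2.8 | 2.2 | 3.2 | 1.2 |

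Stopping at week 6 scores better only if a < 8λ, that is λ > 0.125 for one agent and λ > 0.25 for two.

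The same holds per infusion. With 6 infusions and a 25% event chance at each, a full course scores 6 × 0.25 = 1.5. Stopping one agent after infusion 1, 2 or 3 scores 1.25, 1.50 or 1.75. Stopping two agents after infusion 1 scores 0.25 + 2 = 2.25. The one-agent reversal after infusion 1 needs p + 1 < 6p, so p > 0.20.

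**4. Death.** At an equal event rate, death at week 6 leaves 6/14 = 43% of the expected total. If the 4 weeks before consent were also counted, the figure would be 10/18 = 56%. For contacts at s = 0.5 and u = 0.1, the total is 14 × 0.6 = 8.4 in full and 6 × 0.6 = 3.6 with death at week 6. It is still only 6 × 0.7 = 4.2 if unscheduled contacts double before death.

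At arm level, if a further fraction x of one arm dies halfway, its mean total is multiplied by (1 − x) + 0.5x. For x = 5%, 10% and 15% this is 0.975, 0.95 and 0.925.

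**The case against.** The case against has several sound parts.

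- A reader might infer that adherence generally improves when a patient stops. It does not: each discontinued agent is itself an event. In the per-infusion example only a one-agent stop after infusion 1 beats the full course; a stop after infusion 2 ties, and later stops or two agents score worse. Patients are also approached only after their second week of chemotherapy, so the earliest stops will often precede enrolment.
- A reader might infer that counting ends at withdrawal. The Chart review section says when the review is done, and separately fixes the notes covered at up to 14 weeks after consent. A patient who leaves the study can still have a full record. Only death shortens the count without ambiguity.
- The Utilization section lists its items and does not say that they are added together. It names scheduled and unscheduled contacts separately, so both may be recorded apart. The directional problem arises for any total that pools them.
- An exposure offset or a rule for deaths may be in an analysis plan that is not shown. Its absence from an article is not a defect.
- Under the Methods wording of more appropriate use, recording scheduled contacts and referrals is reasonable.

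These points narrow the concern but leave two things standing. The measure and Hypothesis 1a differ in the text itself, and the adherence definition is fixed as a total although recommended and actual treatment are both abstracted.

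**Conclusion.** The point holds in limited form. The utilisation measure is wider than the hypothesis it serves, and a pooled total would be mostly scheduled contacts under every assumed rate pair. For a patient kept on treatment from week 6 to week 14, the change in such a total ranges from about −0.1 to +7.3 contacts, even with all unscheduled contacts removed.

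The adherence count can misrank an early stop against a completed course, depending on the event rate and the number of agents. Early death lowers it whatever the rate, provided the death adds no charted discontinuation. The arm-level distortion from death is modest: a 10-point excess of deaths halfway through lowers the mean by 5%.

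These sizes rest on assumed constant weekly rates, equal between arms for the death calculation, and on scheduled contacts ceasing when treatment stops. Both outcomes are secondary. The primary symptom score is unaffected. The definitions should be changed, but they do not put the main conclusion at risk.

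**What to change.** **Utilisation.** Make the tested outcome symptom-related hospitalisations, emergency or urgent visits and unscheduled oncology contacts, in line with Hypothesis 1a. Report scheduled contacts and home health or hospice referrals separately by arm. Reconcile the Methods wording with the hypothesis.

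**Adherence.** Define it as actual relative to recommended chemotherapy dose and duration, using what the chart review already records, and report the three event types separately. State how the recommended amount is taken for a patient who dies, because the ratio does not settle that by itself.

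**Exposure and death.** Express event counts per time alive and observed, and show deaths by arm beside both outcomes, so that a low count is not read as benefit. State whether notes from before consent enter the outcome. The choice of count model can stay with the analysis plan.

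**Cost.** Revised outcome wording and a reason-for-contact code on the existing chart form. The nurse already reads the relevant notes, so the added work is coding; the article does not allow that effort to be quantified.

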#### Physical functioning

(source: patient baseline, 10 week, and 14 week surveys) Physical functioning will be measured using the SF-36 summary measure for physical function which has an alpha reliability exceeding 0.80 [36].

#### Utilization of services

(source: medical record audit). The utilization of inpatient and outpatient services will be measured in terms of the number of cancer-related: hospitalizations, visits to emergency or urgent care, scheduled and unscheduled contacts with oncology (in person or by phone), and referrals to home health or hospice.

#### Self-efficacy

(source: patient baseline and 10 week surveys). The Cancer Behavior Inventory

(CBI) Version 2 will be employed to measure patient self-efficacy. The CBI has an internal validity of .94 and covers 7 aspects of self-management, including: maintenance of activity and independence, seeking and understanding medical information, stress management, coping with side effects of treatment, accepting cancer/maintaining positive attitude, affective regulation, and seeking support [37].

#### Social support

(source: patient baseline and 10 week surveys). Two dimensions of social support will be examined: actualized and perceived. Actualized social support will be measured using the Inventory of Socially Supportive Behaviors (ISSB) [38]. The ISSB is a 40 item measure that assesses the receipt of directive guidance (e.g. caregiver suggested the patient take some action), nondirective support (e.g. caregiver expressed concern), positive social exchange (e.g. the caregiver talked with patient about non-cancer related interests), and tangible assistance (e.g. caregiver drove patient to appointment). The ISSB has excellent internal consistency and good test-retest reliability (> 0.90) [38]. Perceived social support will be measured using the Social Provisions Scale (SPS). The internal consistency scores of the six subscales and total scale of the SPS are above .70 and .90 respectively.

### Description of Caregiver Measures

#### Caregiver burden

(source: caregiver baseline, 10 week, and 14 week surveys). The Caregiver Reaction Assessment (CRA) measures 5 dimensions of caregiver burden, including: caregiver esteem, lack of family support, impact on finances, impact on schedule, and impact on health. The CRA has good internal consistency (alpha 0.80-0.90) and a high degree of reliability [39].

#### Caregiver distress (source: caregiver baseline, 10 week, and 14 week surveys)

We will employ the Center for Epidemiological Studies-Depression Scale (CES-D) to measure depression in CarePartners. The CES-D is a scale widely used to measure depression in caregivers because of its ease of use (it has 20 items) and high reliability (alpha = 0.90) [40].

#### Mastery of caregiving

(source: caregiver baseline and 10 week surveys). Caregiver mastery will be measured using the problem solving skill subscale of the caregiver self-efficacy instrument by Zeiss; this subscale has a reliability of .83 [41].

### Quality control

Research assistants rehearse an ATSA call with every patient participant at the time of enrollment. They review call data from ATSA regularly to identify patients who do not respond to scheduled calls. When patients do not respond to multiple ATSA attempts over 48 hours (at any period throughout the 10 weeks of the trial), research assistants contact them to determine the reason; reasons for non-compliance are tracked. Support is offered to patients whose reason for noncompliance relates to technical issues.

Similarly, for the first 4 weeks on the study, caregivers' Web logs are reviewed to identify caregivers who either have not been able to sign-in or create a task list. Research assistants contact caregivers whose Web logs indicate noncompliance and call caregivers to identify the cause. Depending on the reason for the difficulty, research assistants offer to guide the caregiver by telephone during their next online session. Research assistants track all reasons for noncompliance with the website.

Patients and caregivers are not permitted to use ATSA or the website until the baseline survey is completed. Data is entered into a clinical data tracking system that alerts staff of survey due dates and incomplete data. The date the baseline survey is completed determines the dates for the 10 and 14 week surveys. Up to 10 attempts are made to contact each subject or caregiver for scheduling an interview. Abbreviated versions of all interviews are available for patients who have difficulty completing the entire survey. Patients and caregivers receive a $15 gift card for each survey they complete. Monthly updates with comments on completeness of data are maintained and reviewed by the Project Manager.

The success of randomization is monitored quarterly by comparing the demographic and clinical characteristics of patients across study arms. Clinical staff is blinded to the assignment arm, as are the analysts examining the data.

### Monitoring and Reporting of Adverse Events

The study includes several mechanisms for monitoring and identifying adverse events. First, symptom data from ATSA are reviewed weekly by the Principal Investigator (PI) who is a physician. When a patient reports multiple symptoms at severe levels (7 or above), the PI reviews the medical record to insure that the symptoms have been recognized by oncology staff. In the event that there are no progress notes indicating that the patient has been recently seen or contacted, the PI calls the oncology nurse case manager to alert them to the patient's reports.

When patients fail to respond to ATSA calls on two consecutive days, research staff calls the patient to ensure their safety. When patients cannot be reached, study staff informs the caregiver and oncology nurse case manager. Patients who are hospitalized are given the option to suspend their ATSA calls. Patients enrolling in hospice are given the option to come off study.

Subjects and clinicians have access to a toll-free number they can call with study-related problems. Caregivers have access to the research team's contact information through the website. Adverse clinical events are reported immediately to the clinician of record as well as the IRB. All deaths are immediately investigated by a physician not affiliated with the study in order to determine the cause.

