## Abstract

**Background:**

Previous studies have found that cancer patients undergoing chemotherapy can effectively manage their own symptoms when given tailored advice. This approach, however, may challenge patients with poor performance status and/or emotional distress. Our goal is to test an automated intervention that engages a friend or family member to support a patient through chemotherapy.

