During the automated telephonic interaction, the ATSA system gives targeted advice for self-management depending upon the severity of the symptoms reported by the patient. For a severity of three or less, ATSA gives no advice. For a severity greater than three, ATSA refers the patient to the appropriate section of a printed "Symptom Management Toolkit" which the patient receives upon study enrollment. Details about the Toolkit are provided below. When a symptom is reported with a severity of seven or higher, ATSA not only refers the patient to the appropriate section of the Toolkit, but also recommends that the patient contact his/her VA oncology provider. The cut points of 3 and 7 were chosen based on severity scores shown to have similar levels of interference with functioning among patients with cancer [21]. If an ATSA call is not completed at the designated time, the system automatically attempts a repeat call twice at 15 minute intervals. If not completed that day, another call is attempted on the next day at the same time. ATSA stores data on patients' symptom scores as well as the number of attempted call assessments, date/time stamps for all call attempts, and the number of missed call attempts for the purposes of evaluating service usability.

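### The investigator's severe-symptom chart check is meant to confirm recognition of the symptoms, but the stated condition for alerting oncology tests only recent contact

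*Protocol article*

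**What the plan says.** The section Monitoring and Reporting of Adverse Events lists the severe-symptom check first among its mechanisms. It has four parts.

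- **Review.** The article states that "symptom data from ATSA are reviewed weekly by the Principal Investigator (PI) who is a physician".
- **Trigger.** The chart is opened when more than one symptom is reported at 7 or above.
- **Purpose.** At that point "the PI reviews the medical record to insure that the symptoms have been recognized by oncology staff".
- **Escalation.** The event named for escalation is "In the event that there are no progress notes indicating that the patient has been recently seen or contacted". In that event "the PI calls the oncology nurse case manager to alert them".

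A separate route is described under Automated Telephonic Symptom Assessment (ATSA). "When a symptom is reported with a severity of seven or higher", the system points the patient to the Toolkit and also advises contacting the oncology provider. That route needs only one symptom at this level, and it depends on the patient making the contact.

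**The concern.** The purpose and the escalation condition stand in consecutive sentences and test different things. The purpose asks whether oncology staff know about the symptoms just reported. The condition asks whether the chart shows recent contact with the patient. A visit for an infusion, a laboratory result or an unrelated complaint meets the condition and may say nothing about the symptoms.

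The population makes this more than a verbal point. Under Recruitment & Randomization, patients are identified from chemotherapy infusion clinic schedules, so recent notes are to be expected for reasons that have nothing to do with the ATSA report.

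At stake is whether a patient with several severe symptoms is brought to the treating team's attention by the study. The primary comparison of symptom scores is not affected.

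**Working it through.** No arithmetic applies. The article gives no figure for this rule, and none is needed to see the mismatch. The check is to take a patient who meets the trigger (several ATSA symptoms at 7 or above) and compare what the purpose requires with what the condition produces.

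Two facts about the chart decide the outcome: whether it shows recent contact, and whether any note documents the reported symptoms.

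| Recent contact in notes | Reported symptoms documented | Purpose met? | Call under the written condition? | Consistent? |
|---|---|---|---|---|
| Yes | Yes | Yes | No | Yes |
| Yes | No | No | No | **No: an alert is needed and none follows** |
| No | No | No | Yes | Yes |
| No | Yes, in an older note | Arguably | Yes | Errs toward calling |

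The second row is the defect. The symptoms are severe, nothing in the chart shows that oncology staff know of them, and the condition for a call is not met. The fourth row costs at most an unneeded call.

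Two further observations:

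1. The condition does not say that the contact must come after the ATSA report. A contact before the patient reported the symptoms would also satisfy it. The article does not define what counts as recent. That detail may be in the full protocol, and the mismatch does not depend on it: under any window, contact and recognition remain different tests.
2. The ATSA advice does not close the second row. It reaches the patient, and the treating team learns of the symptoms only if the patient acts. The Abstract says that self-management "may challenge patients with poor performance status and/or emotional distress". That is a reason not to rely on this route alone. It does not show that such patients fail to call.

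**The case against.** The strongest reply is that the text is loose rather than defective. It names one event in which the PI calls and does not say that this is the only one. The preceding sentence has a physician read the record for recognition of the symptoms, and a physician who found a note silent on them would presumably act. That is fair as a forecast of good practice. But recognition is the stated purpose and lack of contact is the only stated ground for a call, so the written rule does not secure what the reply assumes.

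A reader might infer several stronger claims. The article does not support them.

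- *Severe reports can reach no clinician, or a single severe symptom is seen by nobody.* All ATSA data are reviewed weekly by a physician, and one symptom at 7 or higher already prompts advice to contact oncology. What is lacking is an assured study-initiated alert to the treating team.
- *The two triggers contradict each other.* One governs automated advice to the patient, the other a physician's chart review. A lower bar for the first and a higher bar for the second can be ordinary tiering. The article does not give its reason, and a sentence would help, but the difference is not an error.
- *Severe scores given in the baseline, 10-week and 14-week interviews are excluded.* The article is silent on them, and a condensed article may leave their handling to the full protocol.
- *The control arm is less protected for reasons unrelated to the intervention.* The caregiver alert is part of the intervention under test, and the PI's review is described without distinction by arm.

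**Conclusion.** The point holds in a narrow form. For patients with several ATSA symptoms at 7 or above, the stated escalation condition does not test the stated purpose of the check. A recent note that does not mention those symptoms leaves the purpose unmet and triggers no call.

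The conclusion rests on one assumption: that staff follow the rule as worded. How often the gap would matter cannot be stated. That would need the share of ATSA calls with several severe symptoms, the frequency of clinic notes, the meaning of recent, and how often notes omit the reported symptoms. The article gives none of these, and a figure built on guesses would not inform the decision.

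The correction is worth making because it is specific, cheap and bears on patient safety. It does not call into question the design, the sample size or the efficacy analysis.

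**What to change.** The investigators should reconcile the two sentences under Monitoring and Reporting of Adverse Events so that the condition for alerting the nurse case manager tests recognition of the reported symptoms rather than contact alone. The exact clinical rule, including any threshold, time window or documentation standard, is theirs to set.

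They may also add a sentence saying why ATSA acts on one symptom at 7 or higher while the PI's chart check requires several.

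The cost is a wording change, somewhat more chart reading by a PI who already reviews these data weekly, and probably somewhat more calls to the nurse case manager. The extra study-prompted contact would arise in both arms.

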#### Primary Analytic Strategy

The primary effect of the intervention will be determined using data obtained at 10 weeks, and the sustained effect will be determined using data obtained at 14 weeks. Cross group comparisons will be made based on an intention-to-treat basis. We will also test the hypotheses with a longitudinal design by fitting a linear mixed-effects modelor a generalized linear mixed effects model to estimate effect averaged over 10 and 14 weeks, adjusting for potential within-person correlation and baseline values of the outcome variables [15].

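### Patients who enter hospice are offered exit from the study, not only from the calls, so any who take it before week 10 would have no survey-based outcome

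*Protocol article*

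**What the plan says.** In the protocol article, the section Monitoring and Reporting of Adverse Events sets two rules side by side. For hospital admission: "Patients who are hospitalized are given the option to suspend their ATSA calls". For hospice: "Patients enrolling in hospice are given the option to come off study". The first pauses one component of the intervention. The second, as worded, is exit from the trial. The article nowhere says that a hospice patient who takes the exit is still offered the follow-up surveys.

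Other sections bear on this:

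- **Outcome source.** Under Description of Patient Measures, summed symptom severity and physical functioning come from patient surveys at baseline, 10 and 14 weeks, and social support from surveys at baseline and 10 weeks.
- **Hospice as an outcome.** Utilization of services, a secondary outcome taken from the medical record, counts "referrals to home health or hospice".
- **Chart review.** The nurse reviews the record "at week 14 or following withdrawal or death". The notes covered run from four weeks before consent to 14 weeks after it.
- **Analysis.** Primary Analytic Strategy states: "Cross group comparisons will be made based on an intention-to-treat basis".
- **Survey burden.** Quality control states: "Abbreviated versions of all interviews are available for patients who have difficulty completing the entire survey".

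**The concern.** Eligibility admits late-stage disease and bars hospice only before enrollment, and both arms continue to receive hospice care as needed. Hospice entry during the 14 weeks is therefore an expected event. It is also a marker of deterioration. Offering study exit at that moment invites missing survey data in patients whose week-10 scores are likely to be among the worst.

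Two things are at stake. If exits are similar in both arms, the week-10 result describes a population without those hospice entrants. If exits differ between arms, the comparison is also biased. In either case the analysis departs from all patients as randomized, and scores that were never collected cannot be recovered at the analysis stage.

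**Working it through.** **1. What is lost and what is kept**

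| Outcome | Source | After hospice exit before week 10 |
|---|---|---|
| Symptom severity (primary) | Patient survey | Lost |
| Physical functioning | Patient survey | Lost |
| Social support | Patient survey | Lost |
| Utilization, including hospice referral | Medical record | Kept, through chart review |
| Chemotherapy adherence | Medical record | Kept, through chart review |

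**2. Whether the planned models can make good the loss**

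- Hypothesis Testing regresses the 10-week score on arm and baseline score. The longitudinal model under Missing Data has the 10- and 14-week scores as outcomes, with baseline values and other covariates as fixed terms. A patient with neither survey has no outcome record in either model.
- A missing-at-random analysis is adequate if, given the model's terms, exit is unrelated to the unseen score. Hospice entry reflects worsening after baseline, so this is doubtful. The weekly call scores might show the worsening, but they are not named as model inputs.
- The pattern mixture fallback applies only if analyses indicate that missingness is tied to unseen outcome values. Observed data cannot show this, so nothing in the data reliably triggers the fallback.

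**3. The plan's attrition figure**

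Inputs from Sample Size Calculation: 224 completing dyads, 25% attrition, 300 enrolled, target difference 0.33 SD.

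- 224 / (1 − 0.25) = 298.7, which rounds up to 299 and reproduces the goal of 300.
- Allowed loss: 300 × 0.25 = 75 dyads.

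The article gives no hospice rate. As an assumption, suppose 5%, 10% or 15% of patients leave this way:

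- 300 × 0.05 = 15, and 15 / 75 = 20% of the allowance
- 300 × 0.10 = 30, and 30 / 75 = 40%
- 300 × 0.15 = 45, and 45 / 75 = 60%

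**4. Possible shift in the contrast**

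Let h_I and h_C be the shares leaving through hospice in the intervention and control arms, and let D be how much worse (higher) leavers would score than stayers, in SD units, the same in both arms. In each arm, mean of all = mean of stayers + h × D. Therefore

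shift (completers' contrast minus all-patient contrast, intervention minus control) = (h_C − h_I) × D.

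Assumptions: every hospice enrollee leaves, D is 0.5 to 1.0, and the shares differ by 5 percentage points.

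- D = 0.5: 0.05 × 0.5 = 0.025 SD, and 0.025 / 0.33 = 8%
- D = 1.0: 0.05 × 1.0 = 0.05 SD, and 0.05 / 0.33 = 15%
- h_I = h_C: shift = 0

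More exits in the intervention arm would flatter the intervention, and more in the control arm would count against it. The formula ignores baseline adjustment, which would remove the part of D already visible at baseline.

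**The case against.** A reader might infer that the sickest patients do drop out, that all their outcome data end, and that exits will differ by arm because the intervention prompts contact with providers. The article does not support this reading, for four reasons.

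- **Exit is optional.** Nothing shows how many would take it. The article does not define the exit as refusing surveys, and withdrawal procedures may be set out in the full protocol.
- **Chart outcomes survive.** The review still takes place after withdrawal, and its note window is tied to consent with no stated cut-off at withdrawal. The hospice referral itself is thus captured. That outcome counts referral, while the exit rule concerns enrollment.
- **The prompt to contact the oncology provider is not specific to one arm.** It belongs to the automated calls, which both arms receive. Only caregiver alerts and website advice differ, so a difference in hospice exits is possible but not shown.
- **The plan does address dropout.** It compares dropouts and their reasons by arm, adjusts if they differ, and names a pattern mixture model.

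It is also fair to say that voluntary withdrawal does not contradict intention to treat, and that some hospice patients would die or be too ill to answer at week 10 under any rule.

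These points limit the concern to survey outcomes and to a possible rather than a demonstrated loss. They do not remove it. Comparing baseline characteristics and reasons for dropout describes the loss without restoring any week-10 score, and an analysis plan cannot recover surveys that were not taken. If the rule is meant only to let patients stop the calls, the sentence says more than is intended and still needs changing.

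**Conclusion.** The point holds in limited form. The hospice rule, as written, offers exit from the study where the hospitalization rule offers only a pause in calls. Patients who take it before week 10 would lack the primary outcome and the other survey outcomes, and this loss is likely to be related to severity. It works against the intention-to-treat aim without contradicting it, and it is better prevented than modelled.

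Its size is unknown. The figures of 0.025 to 0.05 SD (8% to 15% of 0.33 SD) rest wholly on three assumptions: a 5-point difference between arms in exits, exit by every hospice enrollee, and a score gap of 0.5 to 1.0 SD. With equal exits and equal score gaps the shift is zero, though the result then leaves out those who exit. The documents do not support calling this an established bias, or saying that it exhausts the attrition allowance. The change is worth making because it is cheap.

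**What to change.** Reword the hospice sentence under Monitoring and Reporting of Adverse Events so that two decisions are distinct: stopping the automated calls and caregiver alerts, and leaving data collection. A patient who stops the calls should still be offered the abbreviated 10- and 14-week surveys, unless the patient declines or withdraws consent for data collection. Confirm that the abbreviated version contains the eight symptom items, so that the primary outcome can be scored. Record the two events separately, with dates.

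This changes neither clinical care nor the patient's freedom to stop the calls or leave. The cost is a short wording change, one extra tracking field and a few brief telephone interviews. The downside is a small survey burden on very ill patients, who may decline.
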